### Outcomes

2.10

The validated English version for the Mayo Clinic and the Korean version for the Mokhuri hospital will be used for all the outcome assessments. Outcome assessors will be blinded to the allocation results.

The primary outcome will be VAS scores from 0 to 100 for low back pain. The degree of pain will be evaluated on a 100 mm straight line, where the left edge of the straight line will indicate “0: no symptoms,” and the right edge will indicate “100: the most severe pain.” The participant will indicate the average level of lumbar pain experienced for the past week.

The secondary outcomes will include VAS scores from 0 to 100 for leg pain, EQ-5D scores, Oswestry disability index (ODI) scores, Roland–Morris Disability Questionnaire (RMDQ) scores, Zurich Claudication Questionnaire (ZCQ) scores, walking duration and distance without leg pain, a 5-minute treadmill test, the ratio between the actual duration of participation and the originally scheduled duration in each group, the presence of any additional spondylolisthesis treatments, the types of concomitant treatments during the follow-up period, and adverse events (AEs).

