For assessing leg pain, a VAS score from 0 to 100 for leg pain will be assessed. The participant will indicate the average level of leg pain experienced for the past week. The EQ-5D is a common assessment tool for measuring health-related quality of life. It contains 5 dimensions including mobility, self-care, usual activities, pain (discomfort), and anxiety (depression). In this study, we will use the EQ-5D-3L, which has 3 levels of severity for each dimension.^[10,11]^ The ODI consists of 10 topics concerning pain, lifting, ability of self-care, ability to walk, sit, stand and travel, sexual function, social life, and sleep quality and is intended to assess disability and quality of life related to low back pain. ODI scores range from 0 (no disability) to 100 (maximum disability possible).^[12,13]^ The RMDQ is a tool that is widely used for evaluating the functional conditions of patients with low back pain. It contains 24 statements regarding the patient's perceptions about pain and disability, such as physical activity, sleep, psychosocial, and pain frequency. RMDQ scores range from 0 (no disability) to 24 (maximal disability possible).^[14,15]^ The ZCQ is an instrument for assessing pain and symptoms related to spinal stenosis. It consists of 3 domains with 18 questions assessing the symptom severity over the last month, physical functioning over the last month on a specific day, and the patient's satisfaction with current treatment. The results are recorded as a percentage of the possible maximum score, and higher scores represent worse conditions.^[16]^ The walking duration and distance without leg pain and a treadmill test will be used to assess the physical function of the patients. Patients will be asked to walk a distance of 25 m on a round track at their preferred speed, and the distance will be measured when they are no longer able to walk due to pain in the lower limb or lumbar region. For the treadmill test, the participants will walk on the level treadmill at a speed of 1.5 miles per hour, and the time until they start to feel pain in their legs will be measured.^[17]^ The presence of any additional treatments for spondylolisthesis and the types of treatments will be assessed during the follow-up period. Because the treatments in each of the groups will end, patients will be allowed to use additional treatments for spondylolisthesis if they wish to. During this period, participants will be asked whether they used other additional treatments for symptoms related to spinal spondylolisthesis and what types of treatments they used. The ratio between the actual duration of participation and the originally scheduled duration in each group will be assessed as well. Participants whose VAS scores from 0 to 100 for back pain and leg pain decrease below 1 at every weekly evaluation will stop the treatment immediately, according to the early termination rule of this study. The number of patients who stop the scheduled treatments early and the number of those who finish all the scheduled treatments will be assessed in each group, and the differences in the ratio between groups will be assessed. AEs will be assessed during each visit. Participants will be asked to report AEs voluntarily, and researchers will observe participants’ conditions on a regular basis. For each reported AE, the symptoms, signs, starting date, duration, severity, and causal relationship will be assessed by researchers.

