
### Participant time schedule

2.11

At the screening visit, participants will be given detailed explanations of the objectives and contents of this clinical trial and will receive the written agreement form. During this visit, a 5-minute treadmill test, lumbar physical and radiological examinations, ankle-brachial index assessment (or Doppler ultrasonography of lower limbs if necessary), bone mineral densitometer assessment, and inclusion criteria assessment will be conducted. If the participant can be enrolled in the study, random assignment of the participant will take place at the following visit. Before the treatments begin, the VAS scores for low back pain and for leg pain, EQ-5D scores, ODI scores, RMDQ scores, ZCQ scores, walking duration and distance free of leg pain, and a treadmill test will be assessed. After that, participants will undergo 10 treatments over 5 weeks. After treatment, evaluations will be performed immediately (7 weeks) and at 18 weeks, 30 weeks, 54 weeks (1-year follow-up), and 102 weeks (2-year follow-up). AEs will be assessed at each visit (Table 1).

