### Sample size

2.12

To calculate the sample size, a retrospective study performed on 44 patients with lumbar spinal spondylolisthesis^[8]^ and the previous clinical trial data that assessed physical therapy for hospitalized patients in a similar study setting^[18]^ were used. To determine a meaningful difference between groups, a minimal clinically important difference of 2.5 points on the numeric rating scale of 0 to 10 was used.^[19]^ The standard deviation (SD) was 4.65 from the abovementioned previous studies. For the sample size calculation, the significance level (α) was 0.05, and the power (1–β) was 0.80. The following formula was used for the calculation. Assuming a drop-out rate of 10%, 61 participants will be needed in each study group, yielding a total of 122 participants needed for this study. 
[figure not shown]

In terms of the total 122 participants in the study, 108 participants will be recruited at the Mokhuri Oriental Medicine Hospital and 14 participants at the Mayo Clinic.

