### Statistical analysis

2.13

Statistical analysis will be performed based on an intention-to-treat analysis for the assessment of effectiveness outcomes and a per-protocol analysis for the assessment of safety. The missing values will be substituted with the most recently observed value (the last observation carried forward method). For the demographic information, continuous data will be presented as the mean and SD, and categorical data will be reported with a frequency table. The 2-sample *t* test (or Wilcoxon rank-sum test) will be used for the analysis of continuous variables after evaluating the data distribution. For categorical data, the chi-square test (or Fisher exact test) will be used. Outcome variables including VAS scores for lumbar pain and leg pain, EQ-5D scores, ODI scores, RMDQ scores, ZCQ scores, walking duration and distance without leg pain, and the treadmill test will be summarized with means and SDs. For statistical analysis of continuous outcomes, changes in the scores before and after treatments will be regarded as dependent variables, with the baseline scores and research institutions as covariates and the groups as fixed factors, to perform the analysis of covariance. To verify the trends for each visit in the 2 groups, repeated measures analysis of variance will be performed. For categorical outcome data, the chi-square test (or Fisher exact test) will be used.

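### Carrying the last answer forward turns a dropout's last 'no' on additional treatment into 'untreated to week 102', which under-counts use and biases the arm comparison if loss differs by arm

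*Protocol article*

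**What the plan says.** The Outcomes section (2.10) lists among the secondary outcomes "the presence of any additional spondylolisthesis treatments, the types of concomitant treatments during the follow-up period". It explains that once study treatment has ended "patients will be allowed to use additional treatments for spondylolisthesis if they wish to", and that in this period "participants will be asked whether they used other additional treatments for symptoms related to spinal spondylolisthesis and what types of treatments they used". No date of first use is mentioned.

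The Participant time schedule (2.11) sets the visits: "evaluations will be performed immediately (7 weeks) and at 18 weeks, 30 weeks, 54 weeks (1-year follow-up), and 102 weeks (2-year follow-up".

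The Statistical analysis section (2.13) has one rule for missing data, with no exception for any outcome: "The missing values will be substituted with the most recently observed value (the last observation carried forward method". Its only method for categorical outcomes is: "For categorical outcome data, the chi-square test (or Fisher exact test) will be used". The one longitudinal method it names, repeated measures analysis of variance, is not suited to a yes/no event.

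**The concern.** Starting an additional treatment is an event that can happen at any time up to the last visit. Once it has happened it stays true; until then, 'no' is only an answer so far. A 'no' at week 18 carries no information about weeks 18 to 102. LOCF nevertheless turns it into a definite 'no' at week 102. For any use by week 102 the error runs one way, towards too little use, and it grows with the number lost and with how early they leave.

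If both arms lose participants at the same rate and have the same true use, the error cancels. If loss differs, the arm with more loss appears to need less additional treatment. The treatments are visibly different, and section 2.10 mentions blinding only of outcome assessors, so unequal loss is possible, though the article gives no evidence of it. Additional treatment is unrestricted after the treatment period, so this outcome also bears on how the long-term pain results are read.

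**Working it through.** **The plan's own figure.** The article gives no expected rate of additional treatment, so there is nothing to reproduce for this outcome. The number per arm can be checked. With a difference of 2.5, a standard deviation of 4.65 and "the significance level (α) was 0.05, and the power (1–β) was 0.80" (taken as two-sided), n = 2 × (4.65 × (1.960 + 0.842) / 2.5)² = 54.3 per arm. Then 54.3 / 0.9 = 60.3, rounded up to the stated 61. I use 61 per arm below.

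**Assumptions, none of them from the article.**
- True use by week 102 is P = 60% in both arms.
- The hazard of first use is constant over the 96 weeks of follow-up (the 96 is from section 2.2).
- Loss is uniform over that period and independent of use.
- The outcome is any use by week 102.

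**Step 1: what LOCF records.** Cumulative hazard H = −ln(1 − 0.60) = 0.916. A dropout is credited only with use before leaving, on average 1 − P/H = 1 − 0.60/0.916 = 34.5%, instead of 60%. With a fraction d lost, observed use = (1 − d) × 60% + d × 34.5%, a shortfall of 25.5 points × d.

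| Loss d | Observed use | Shortfall |
|---|---|---|
| 5% | 58.7% | 1.3 points |
| 10% | 57.5% | 2.5 points |
| 15% | 56.2% | 3.8 points |
| 30% | 52.4% | 7.6 points |

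**Step 2: the arm comparison.** The true difference is zero.
- Equal loss: 0 points.
- 5% vs 15% (average 10%, the planned dropout rate): 0.255 × 10 = 2.5 points.
- 10% vs 30%: 0.255 × 20 = 5.1 points.

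**Step 3: use known only from the last attended visit.** Step 1 credits use up to the moment of leaving. Now count only use reported at the last visit attended. Weeks 18, 30, 54 and 102 fall at 12, 24, 48 and 96 weeks of follow-up, and anyone lost before week 18 is taken as a 'no' from week 7. With hazard 0.916/96 per week, cumulative use at 12, 24 and 48 weeks is 10.8%, 20.5% and 36.8%. The average credited to a dropout is (12 × 0 + 12 × 10.8 + 24 × 20.5 + 48 × 36.8)/96 = 24.8%. The shortfall becomes 35.2 points × d, and the spurious difference 3.5 points (5% vs 15%) or 7.0 points (10% vs 30%).

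**Step 4: against sampling error.** The standard error of the difference at 61 per arm is about √(2 × 0.574 × 0.426 / 61) = 9.0 points. On the Step 1 figures, a nominal 5% test would reject about 6% of the time at 5% vs 15% loss and about 9% at 10% vs 30%.

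**Step 5: when use truly differs.** With true use of 40% and 60% and a constant dropout hazard, the true 20-point difference is observed as 19.3 points at 10% loss in each arm. It becomes 17.0 or 21.5 points when loss is 5% in one arm and 15% in the other, depending on which arm loses more, and 13.7 or 23.2 points at 10% and 30%.

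**Step 6: power.** In the 40% vs 60% case with 10% loss, chi-square has about 57% power and a log-rank test about 61% (hazard ratio 0.557, about 58 events). The gain is modest.

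**The case against.** The strongest reply is that the point is small. At the planned 10% dropout, balanced across arms, each arm is under-counted by about 2.5 points at 60% use and the comparison is not distorted when true use is equal. The 10% vs 30% case averages twice the planned loss, and nothing in the article suggests arm-dependent loss. A proportion is a legitimate summary of presence of additional treatment. The trial was sized on pain, and this outcome is underpowered by either method. All of that stands and limits the weight of the point. It does not make LOCF a sound rule for this outcome.

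The article also does not say whether use is analysed cumulatively or visit by visit. Visit by visit, LOCF would carry a stale 'yes' as well as a stale 'no', so the direction of error would be less clear and the objection about lost timing weaker. A last answer would still be filled in for periods nobody asked about.

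Three stronger readings are tempting, and the article does not support them:
- **Every dropout is counted as never treated.** Only those whose last answer was 'no' are; an earlier 'yes' stays 'yes', and someone lost before any answer has nothing to carry forward.
- **Overlapping treatment types are tested as one category variable.** The coding of types is not given. They may be tabulated or tested one by one, and an article may leave that to the full protocol or analysis plan.
- **Chi-square wastes much power here.** A sizeable gap needs near-universal use. In simulations with 55 per arm, no loss and hazard ratio 0.6, it is 43% vs 46% at 60% control use and reaches 51% vs 67% only at 95%. The article gives no basis for use that high.

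**Conclusion.** The concern holds as a minor point on one secondary outcome. Two rules that section 2.13 states outright, LOCF for all missing values and chi-square or Fisher for categorical outcomes, together record a participant lost after a 'no' as untreated to week 102. Any use by week 102 is then under-counted, and the comparison is biased to the extent that loss differs by arm.

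Under the assumed 60% use in both arms, the spurious difference is about 2.5 to 3.5 points for 5% vs 15% loss, 5 to 7 points for 10% vs 30%, and zero for equal loss. These sizes rest on assumed rates of use, a constant hazard and uniform loss; the direction for cumulative use does not depend on the particular rates. The case for change is bias from unequal follow-up, not power.

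**What to change.** In section 2.13, exempt this outcome from LOCF and define it as time to first additional spondylolisthesis treatment over follow-up, censored at the last visit at which use was asked. Because use is asked at visits, analyse it by visit interval: a discrete-time (complementary log-log) model with arm and institution, or Kaplan-Meier curves with a log-rank test stratified by institution. The proportion using any additional treatment by week 102 can then be read from the curve, so the present summary is kept.

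The cost is a few sentences. No new data are needed, since the visit interval suffices. There are two downsides. Start times are known only to the interval, and the last interval is 48 weeks (54 to 102). Censoring assumes that dropout is non-informative given arm and institution, so loss by arm and visit should be reported next to the result.

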### Ethics

2.14

Approval from each institutional review board has been obtained for the protocols before the start of this study (institutional review board application number: MHNBH-16031 at the Mokhuri hospital and 15-008457 at the Mayo Clinic). Prior to the clinical trial, the participants will provide written informed consent for participation in the study.

## Discussion

3

This is a multinational, multicenter study protocol for a clinical trial assessing the effectiveness and safety of nonsurgical integrative interventions for symptomatic lumbar spondylolisthesis. Conservative interventions are regarded as effective in most lumbar spinal spondylolisthesis patients, but there are no appropriate options other than spinal surgery for patients who have continuing symptoms after conservative treatment.^[20]^ As surgery is not always promising for all patients, new nonsurgical therapeutic options need to be explored for this population.

This multinational study will ensure generalizability of the study results. This is the most important strong point of this study. Generalizability is an important issue when implementing the results of studies into clinical practice. An randomized controlled trial, which can reduce the risk of bias in study participant selection, may not be able to ensure external validity if the study population is limited to homogeneous group under strict eligibility criteria.^[21]^ From this perspective, a multinational, multicenter clinical trial has benefits of ensuring generalizability because patients with diverse regional and ethnic characteristics are recruited.

One important limitation of this study is its lack of internal validity. Researchers with different levels of clinical experience and educational backgrounds will participate in this study, so internal validity between the 2 research institutions may be a potential problem. To protect against potential bias from this aspect, we generated a common SOP for treatments and conducted 1 month of an integrated education program for researcher proficiency.

Hopefully, this study will provide clinical evidence on nonsurgical integrative interventions for symptomatic spondylolisthesis.
